## Abstract

Tungiasis, a World Health Organization neglected tropical disease, is caused by the female sand flea. Most clinical trials for tungiasis use expensive or impractical drugs, which are difficult for residents to use. However, in western Kenya, communities successfully treat tungiasis with sodium carbonate. We hypothesise that the topical risk-difference of 5% sodium carbonate is no more than 10% non-inferior to dimeticone (NYDA^®^) for tungiasis treatment. This is a protocol for a non-inferiority study, which will be randomised and with an observer-blinded control. The study will have two arms: 5% sodium carbonate and NYDA^®^, one on each foot, and will take place at state primary schools in Homa Bay County, Kenya. Fleas identified among school children aged 8–14 years with sand-flea lesions will be enrolled in the study. For each participant, the viability of the embedded fleas, clinical signs including inflammation, and symptoms will be monitored for seven days after treatment. The proportion of dead fleas will be compared in the primary analysis. All adverse events will be monitored throughout the study period. We expect to identify the most effective treatment between sodium carbonate and NYDA^®^ for tungiasis, which can be adopted in the community.

## 1. Introduction

Tungiasis is a cutaneous parasitosis caused by the female sand flea *Tunga penetrans* [1], which is distributed in tropical and subtropical regions of the world. Tungiasis is prevalent in Africa and is recognised as a neglected tropical disease by the World Health Organization (WHO) and has also been predicted to be a target for future priority measures (Sankei-photo, 2019). *Tunga penetrans* is a unique species within the realm of fleas, in that non-fertilised females penetrate the skin and remain there until they die in situ after 4–6 weeks [2,3]. It is one of a few parasites that can maintain its life cycle within sleeping quarters and is capable of completing its life cycle indoors in dwellings without a solid floor [4]. Its eggs are expelled and fall directly to the floor when an infected person sleeps, or later when the bed is made. When the floor is swept, the eggs may be transferred to crevices and holes that contain sufficient organic matter for larval development. Adults emerging from pupae adhere to and penetrate the skin when a person places their bare feet on the dwelling floor [5].

Its age-specific prevalence shows a characteristic pattern, with a maximum prevalence in the elderly population and children aged 5–14 years [6]. Children with tungiasis are reported to have disproportionately high levels of absenteeism from school and perform worse academically than unaffected pupils, because constant itching and pain make it difficult for them to concentrate on schoolwork [7].

### Treatment Options for Tungiasis

If not managed properly, infestation by *Tunga* fleas, commonly known as jiggers, can result in health and socio-economic effects. The surgical extraction of embedded sand-fleas is common, but has several shortcomings. People living in endemic areas may use safety pins, needles, scissors, knives, or sharpened pieces of wood [8]. It is time-consuming and painful, and often results in infections as well as secondary infections such as tetanus, HIV, and hepatitis B and C. One study in sub-Saharan African children showed that inadequate treatment of jiggers is a source of hepatitis B and C transmission [9,10]. Individuals may also abstain from treatment due to the associated pain. Antibiotics and anti-tetanus toxins must be applied to treat secondary infections after jigger removal, and this is often an unmanageable expense.

The Kenyan guidelines [11] recommend the use of antiseptic solutions, including Savlon, potassium permanganate, and hydrogen peroxide followed by petroleum jelly. Flea repellents include N, N-Diethyl-meta-toluamide, Zazarin (coconut oil), neem and coconut oil preparations, jojoba oil, and aloe vera extract. Silicone oil (dimeticone) is also strongly recommended, since it is a more effective and non-toxic remedy. Trends in the use of therapeutic agents have changed significantly in the last eight years. There is ongoing research into therapeutic agents, compounding methods, and application methods, with a focus on increasing the availability of inexpensive treatments without side effects such as pain and itching. Current studies are focusing on the quality of life for patients and the use of naturally derived treatments. A manual search and literature search of PubMed and MEDLINE (EBSCOhost) without language restriction resulted in 141 initial references, from which we finally selected nine relevant articles which showed 13 different treatments. Six randomised control trials and three intervention studies have studied treatments related to tungiasis. Studies are being carried out mainly in South America and East Africa.

#### Locally Available Treatments

Most clinical trials for tungiasis have studied expensive or impractical drugs such as ivermectin, metrifonate, and dimeticone, which are difficult for residents to use on a sustainable basis. In Kenya, however, communities have been successfully treating tungiasis with a herbal-formula lotion composed of neem seed and coconut oils [12]. A recent study conducted in coastal Kenyaby Elson et al. (2019) showed that although 20% neem plus coconut oils did not kill more fleas than potassium permanganate within seven days, it resulted in better secondary outcomes. Specifically, the acute symptoms were much reduced and children had higher odds of being pain-free. Another interventional study [13] was conducted in Muranga County, using 100% coconut oil. However, due to the short observation period of that study, it was unclear whether the fleas died according to their natural lifecycle or due to the intervention. The aforementioned are common local treatments in eastern Kenya, but not in western Kenya, which is far from the ocean. In western Kenya, a local practice is to use sodium carbonate, locally referred to as Magadi or Magadi soda. This naturally available chemical is used in industries for manufacturing glass, cake glazing, as an anti-caking agent for pastries, and within chemical detergents applied for various purposes in homes. Kenyan communities use Magadi to soften green vegetables and meat during cooking. It sells on the local market at approximately KES 10 (USD 0.08) for 50 g. A study conducted in 2016 demonstrated its effectiveness in Siaya County, Kenya [14] and was published after the National Policy Guideline of recommended treatments was developed in 2014. The study of sodium carbonate did not perform practical comparisons, but concluded that it has some degree of effectiveness as a treatment. There is a need to conduct a comparative study prior to including sodium carbonate within the government-recommended treatments. 

Dimeticone is strongly recommended by the WHO for the treatment of tungiasis. A study conducted in Kenya showed that dimeticone applied to the feet up to the ankles killed 78% of embedded sand-fleas within seven days [15]. At an informal meeting of the WHO/Pan American Health Organization in 2021 experts recommended dimeticone as the standard treatment for tungiasis, and it is the only topical treatment that is indicated on the WHO tungiasis website. In addition, the previous review article also concluded that there was sufficient evidence for the dimeticone-based product [16], and increased its availability in Kenyan health facilities. However, it is expensive and not available elsewhere in the local area. 

Sodium carbonate is said to emulsify and remove fat and secretions on the surface of the skin [17]. It has long been used in food preparation and medicine and is safe for humans. In Tanzania, sodium carbonate contaminated with fluoride has been reported to cause fluorosis in human teeth, for instance, when used to tenderise meat [18]. Trona is mined in Kenya, is the source of almost pure sodium carbonate, as well as Magadi soda, and is not contaminated with fluoride [14]. Inhalation of sodium carbonate can lead to adverse effects such as respiratory-tract irritation, cough, shortness of breath, and pulmonary oedema. When using sodium carbonate, care must be taken to avoid ingestion or inhalation of the powder, and to allow for the free flow of fresh air. Accidental or intentional overexposure to sodium carbonate may occur via the oral route. However, a study of acute oral toxicity did not report high toxicity, due to the neutralisation of carbonate in the stomach to bicarbonate and/or carbon dioxide [19]. Contact with eyes can provoke a burning sensation. To avoid these potential hazards, in this study sodium carbonate will be handled with care, and we will choose open preparation workplaces with good airflow.

NYDA^®^ contains two dimeticones or silicone oils with different viscosities and a high creeping property. In many European countries, it is commercialised as a medicinal product for the treatment of head-lice infestation, and is produced by G. Pohl-Boskamp GmbH & Co. KG, Hohenlockstedt, Germany [20,21]. The extremely low viscosity (100 cSt) of NYDA^®^ enables it to penetrate the trachea (respiratory airways) and thereby suffocate the embedded insect. Dimeticones are safe, since they are biochemically inert, non-toxic, non-carcinogenic, and non-teratogenic [22,23]. Due to the physical mode of action of dimeticones, it is highly unlikely that sand fleas would develop resistance. The only disadvantage of the agents is that they are inflammable; thus, it is recommended that individuals should stay away from fires for up to 2 h after application [24].

This is the research protocol: in this study, we compare experimental (dimeticone) and local (sodium carbonate) treatments, aiming to assess the non-inferiority of local treatments of tungiasis among children, who are the key target-population of this disease. In addition, we will investigate further treatment strategies that apply to the local area.

**Hypothesis:** 
*In this study, we hypothesise that the topical risk-difference of 5% sodium carbonate is no more than 10% non-inferior to dimeticone (NYDA^®^) when used in the treatment of tungiasis.*

Figure 1 shows the non-inferiority margin and the relationship with 95% confidence interval (95% CI) of the difference between experimental and control groups. If the risk difference of cure rate (95%CI) is greater than −10%, it can be shown than 5% sodium carbonate is not inferior to NYDA^®^.

## 2. Experimental Design

### 2.1. Objectives

Main objective: To compare 5% sodium carbonate and dimeticone in the treatment of tungiasis among children in Kenya.

Specific objectives:(1)To compare the cure rates of the two treatments (5% sodium carbonate and dimeticone) within seven days.(2)To assess the safety of the two treatments by determining the incidence of adverse effects.(3)To compare the acute pathology scores of the two treatments.(4)To assess the acceptability of the two treatments in the community.

### 2.2. Justification

In this study, we will compare two treatments for which effectivities have been evaluated and studied in Kenya. Sodium carbonate is available in the local market, whereas NYDA^®^ (a mixture of two dimeticone oils with different viscosities and spreadability) is not yet available in the Kenyan market. The advantages and disadvantages are shown in Figure 2. In terms of mechanism of action, sodium carbonate can soften the tissue and push fleas out by allowing chemicals to enter the body of the flea, due to changes in osmolarity and swelling [14], while dimeticone can penetrate the abdominal cone of fleas, killing them. According to a previous proof-of-principle study [15] the mechanism of action of dimeticone is purely physical. The substance occludes the tracheae of *T. penetrans*, resulting in parasite death.

Solutions of sodium carbonate, typically containing 1% water, are used in personal skin-care products. Application to the feet results in an exposed surface area of 1120 cm^2^ (TGD, Part I, Annex VI). Considering a film thickness of 100 µm and a percutaneous absorption of 0.1%, the amount of sodium carbonate absorbed via the skin would be 0.1 mg. Assuming an exposure time of 20 min, this would amount to 0.0014 mg per application. The estimated systemic dose of sodium carbonate would be equal to 0.0014/60 = 2.3 × 10^−5^ mg/kg body weight [19]. Therefore, the exposure to sodium carbonate via the method of soaking a foot in a 0.5% sodium carbonate solution for 15 min, which is planned for this study, can be regarded as negligible.

### 2.3. Study Design

The study will utilise a randomised design, compared to standard treatment intervention. Figure 3 shows the flowchart of this study. It will have two arms: treatment of embedded sand-flea infestations with 5% sodium carbonate, versus dimeticone. Randomisation will be performed according to treatment. A non-inferiority design is chosen, since it would be unethical to withhold an existing treatment that has demonstrated efficacy. This study will not measure any environmental intervention; therefore, we can measure only efficacy, not effectiveness. All participants will receive both treatments, one on each foot. Therefore, it is not possible to blind participants and interveners to treatment-group assignments. The study will be conducted during the dry season, when the prevalence of tungiasis is known to be at its peak, and at a time not impacted by holidays.

### 2.4. Study Area

The study will be conducted at state primary schools in Homa Bay County, Kenya. The study county has eight sub-counties, among which Ndhiwa and Suba South have been chosen for this study, due to the high prevalence (1.1%) of tungiasis in those areas.

### 2.5. Study Population 

The study will recruit children aged 8 to 14 years. Children will be included if diagnosed with *Tunga penetrans* infestation and manifesting symptoms and signs characteristic of tungiasis and classified as Fortaleza stage II or III [2].

#### 2.5.1. Eligibility Criteria

Children aged 8 to 14 years who have been infected with tungiasis in Homa Bay, Kenya (the most commonly affected age-group, and who can reliably answer questions).Children and caregivers who provide written assent and consent to participate in the study.Children who have more than one lesion of embedded sand-fleas that are independent (not clustered) and easily observable, on both feet.

#### 2.5.2. Exclusion Criteria 

Children infected with more than twenty fleas. These are defined as severe cases [25] and need to be immediately referred to the nearest health facility for treatment or to the medical doctor cooperating in this research, for consultation.Children/caregivers who decline to participate.Children with other pruritic skin-conditions on the foot.

### 2.6. Outcome Measures

The primary endpoint is the cure rate on day seven, following treatment with either 5% sodium carbonate solution or dimeticone. Embedded fleas will be assessed using a digital handheld microscope at the baseline, and on days 3, 5, and 7 for four signs of viability: expulsion of eggs, excretion of faecal thread, excretion of faecal liquid, and pulsations/contractions. An embedded flea will be considered non-viable if none of the four signs of viability is detected during 15 min of observation.

Secondary endpoints are adverse effects (nausea/vomiting, arthralgia, fever, headache, fatigue/malaise, myalgia, and chills), acute pathology scores (assessing pain, itching, erythema, warmness, oedema, desquamation, fissure, suppuration, ulcer, abscess, and lesions in clusters), and differences in feeling and ease of children during the 7-day period after the treatments. Each participant will also be asked to rate their experience of pain and itching using a quick help-sheet with illustrations. An inflammation score [15] will be used for this assessment.

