## 3. Procedure

### 3.1. Sampling and Recruitment

A multi-stage sampling method will be used in this study. Stage 1 will involve the sampling of sub-counties, stage 2 will involve the sampling of schools, participant selection will be performed in stage 3, and stage 4 will involve the sampling of embedded sand-fleas.

Stage 1: Sampling of sub-counties:

Ndhiwa and Suba South sub-counties will be sampled because they have the highest number of reported cases of tungiasis in Homa Bay County. 

Stage 2: Sampling of schools:

Primary schools in the study area are ranked according to the number of reports made to the Health Department. Therefore, we will visit schools in areas with the highest number of reported cases and with the highest number of affected students, in order. 

Stage 3: Sampling of participants:

In each school, children aged 8 to 14 years will be selected in descending order of grade. At the beginning of the study, a sealed envelope will be used to randomise the two treatments. In the sealed envelopes will be written “Right foot: dimeticone, Left foot: 5% sodium carbonate” or “Right foot: 5% sodium carbonate, Left foot: dimeticone” with a participant number. Before randomisation, lesions will be sampled to avoid selection bias.

Children will be informed not to manipulate the lesions during the next 7 days. Children whose skin conditions are suspected to be due to tungiasis by teachers, caregivers, and healthcare workers (including community health-volunteers) will be screened for eligibility to participate in this study. Such children and their caregivers will then be contacted by the local co-investigator and their field assistants to ask if they are willing to participate in the study, after explaining the study objectives and procedures. Informed consent from caregivers and assent from children will be obtained after both agree to participate. Participants will be randomly selected until the point of saturation is reached.

Stage 4: Sampling of embedded sand-fleas:

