### 3.5. Data Collection and Storage

Data will not be collected on the names and affiliations of the participants. If they wish to discontinue the interview, observation, and treatment, their decision will be respected without any objections. Participation of school children in this study is totally voluntary. Since this is a school-based study, consent will first be obtained from each school. Informed consent will then be obtained from each participant, in accordance with the Ottawa Statement, an international guideline for cluster-randomised trials. For lesions not studied, dimeticone will be applied later, if desired. The area to be observed will be marked with an oil-based pen and photographed with a smartphone. Video recordings with a smartphone will be made only at the time of intervention, to confirm the intervention method. During the treatment, skin symptoms will be monitored until the final decision on the 7th day, using a checklist. Lesions will be examined and staged according to the Fortaleza classification [2], and counted (live/dead). The cure rate will be calculated at each stage, and significant differences at each stage will be tested. Participants will be observed and queried about adverse effects, and the severity score will be used to assess symptoms of acute tungiasis, including pain and itching. Feeling and ease of each treatment will be assessed using a questionnaire. Trained nurses will monitor the participants, and interviews will be conducted under the guidance of a medical doctor at treatment initiation and during the final decision. 

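### The primary outcome does not separate a flea dead in the skin from one no longer in the lesion, although the plan says sodium carbonate can push fleas out

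*Protocol article*

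**What the plan says.** All references are to the protocol article.

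- **Endpoint by name.** Section 2.6: "The primary endpoint is the cure rate on day seven, following treatment with either 5% sodium carbonate solution or dimeticone". The Abstract names it differently: "The proportion of dead fleas will be compared in the primary analysis".
- **Scoring rule.** Section 2.6 lists four signs (egg expulsion, faecal thread, faecal liquid, pulsation or contraction), looked for at baseline and on days 3, 5 and 7, and then states: "An embedded flea will be considered non-viable if none of the four signs of viability is detected during 15 min of observation".
- **Recorded states.** Section 3.5: "Lesions will be examined and staged according to the Fortaleza classification [2], and counted (live/dead". No third state is given.
- **How the treatments act.** Section 2.2: "sodium carbonate can soften the tissue and push fleas out by allowing chemicals to enter the body of the flea", whereas "dimeticone can penetrate the abdominal cone of fleas, killing them".
- **Manual removal.** The Introduction, under treatment options, describes surgical extraction as common. Section 3.1 gives one safeguard: "Children will be informed not to manipulate the lesions during the next 7 days".
- **Missing data and analysis set.** Section 4.1 uses multiple imputation and a per-protocol approach. It does not say whether a lesion whose flea has gone is missing, excluded, dead or cured.

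**The concern.** Every one of the four signs needs a flea to be present. Section 3.1 (stage 4) enrols only lesions with viable embedded fleas and has each one circled and photographed, so the marked spot will be examined again even if the flea has gone. It will show no sign, and of the two recorded states only *dead* is a ready fit.

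Two consequences follow. First, the plan itself attributes expulsion to the test treatment and not to the comparator, so empty lesions could be more frequent on the sodium carbonate foot. If the outcome is flea death, any live expulsion scored as dead raises that rate alone. Second, a flea dug out by the child or a caregiver would be credited to whichever treatment that foot received, which pulls the two rates together.

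In a non-inferiority trial with a 10-point margin, both errors lean towards the claim. The blinded observer in section 3.2 gives no protection, because the difficulty lies in the recorded categories. If absence is not noted at the visit, it may not be recoverable later.

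**Working it through.** **The plan's own figure first.** Section 2.8 assumes 80% in both arms, margin 10 points, 90% power, α = 0.05, design effect 1.5 and 10% loss.

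- n = (1.645 + 1.282)² × 2 × 0.80 × 0.20 / 0.10² gives 275 per arm.
- 275 × 1.5 gives 413, and 413 / 0.9 gives 459. The stated 460 is reproduced, with α taken as one-sided 0.05.
- Section 4.1 tests at one-sided 0.025, so both levels are shown below.
- Effective n per arm after loss and design effect: 460 × 0.9 / 1.5 = 276.

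**Live expulsions scored as dead.** The documents give no expulsion rate, so x is an assumption: the share of sodium carbonate lesions whose flea leaves alive and is scored dead, with none on the dimeticone foot. True kill rates are set at 70% v 80%, exactly on the margin. By the normal approximation:

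P(claim) = Φ((0.10 + p_obs − 0.80)/SE − z), with p_obs = 0.70 + x and SE = √[(p_obs(1 − p_obs) + 0.16)/276].

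For x = 0.05: SE = √(0.3475/276) = 0.0355, and 0.05/0.0355 − 1.96 = −0.55, so P = 29.1%.

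| x | observed difference | claim at 0.025 | claim at 0.05 |
|---|---|---|---|
| 0 | −10 points | 2.5% | 5.0% |
| 2 points | −8 | 8.0% | 13.7% |
| 3 points | −7 | 13.0% | 20.9% |
| 5 points | −5 | 29.1% | 40.7% |
| 10 points | 0 | 83.6% | 90.2% |

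**Empty lesions dropped instead.** With x = 5 points, the observed sodium carbonate rate is 0.70/0.95 = 73.7%, a difference of −6.3 points. With 276 × 0.95 = 262 lesions in that arm, SE = 0.0363 and P = Φ(0.0368/0.0363 − 1.96), about 17% at one-sided 0.025. Imputing them from the lesions that were observed would lean the same way.

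**Manual removal.** Suppose a share m is removed on both feet, regardless of viability, and d is the true difference.

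- Counted as cures, each rate becomes p + m(1 − p), and the difference is (1 − m)d.
- Counted as failures, each rate becomes (1 − m)p, and the difference is again (1 − m)d.
- Left out of the analysis, each rate stays at p and the difference stays at d.

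With m = 10%, −10 points becomes −9 (73% v 82%), and the false-claim rate rises from 2.5% to about 4.7% at one-sided 0.025. Rescoring removals as failures does not undo this. Leaving them out does, provided removal is unrelated to viability.

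**If expulsion is a legitimate cure.** Take 80% in both arms, with 5 of the 80 points on sodium carbonate achieved by expulsion. Scoring those as failures gives 75% v 80%, and the chance of a correct claim falls from 84% to 29% at one-sided 0.025 (from 90% to 41% at 0.05). The choice of definition therefore matters in both directions.

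**The case against.** A reader might infer that the plan scores an absent flea as killed, so that the primary outcome is biased towards sodium carbonate. The text does not support that.

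- The rule in section 2.6 is worded for an embedded flea, and one that has left the skin is no longer embedded. Dead, missing and excluded are all open readings. That dead is the most natural one is an inference from the live/dead count.
- The endpoint named in section 2.6 is cure, and sections 2.8 and 4 also speak of cure. A lesion emptied by the treatment may fairly be called cured, in which case counting it as success is no error.
- Section 2.2 says only that sodium carbonate *can* push fleas out. It gives no frequency and does not say that they leave alive. The same sentence has chemicals entering the flea's body.
- Manual removal is partly addressed by the instruction to children and by the marking and photographs. Section 3.4 mentions a case record form that is not shown and may hold more detail.

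These points stand, and they limit the claim. They do not remove it. Which events count as success belongs to the definition of the primary outcome, and the article uses two names whose meanings can differ for a flea that has gone. Reading empty lesions as excluded or imputed would also favour sodium carbonate if some fleas leave alive.

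**Conclusion.** The point holds as a gap in the outcome definition. The plan scores live or dead by absence of signs, uses *cure* and *dead* interchangeably, and has no stated place for a flea that is no longer in the lesion, while itself expecting expulsion from one treatment and calling extraction common.

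The direction is conditional. If the outcome is flea death and some fleas are expelled alive, counting empty lesions as dead favours sodium carbonate. Manual removal credited to treatment pulls the difference towards zero. If the outcome is cure and includes expulsion, the first effect is not a bias.

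The size cannot be known from the document. The 29% figure is an illustration. It assumes x = 5 points, no live expulsion on the dimeticone foot, a true difference exactly at the margin, the plan's design effect and a two-sample normal approximation. It shows that a few points of misclassification matter against a 10-point margin, and is no evidence that such misclassification will occur.

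**What to change.** 1. On days 3, 5 and 7 record one of three states for each marked lesion: in situ viable, in situ non-viable, or absent. Add evidence of manual removal, yes or no.
2. Use one name and one definition for the primary outcome throughout, stating whether a flea expelled without manipulation counts as success.
3. Do not credit manually removed fleas to treatment. One way is to treat them as protocol deviations outside the per-protocol set, with counts reported by foot. Rescoring them as failures would leave the same attenuation.
4. Report a sensitivity analysis with absent fleas scored the other way.

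The claim should not be made to depend on success under both scorings. If expulsion is a genuine cure, that would penalise sodium carbonate for its stated mechanism and, at 5 points of expulsion, cut the chance of a correct claim from 84% to 29%.

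The cost is one extra field on the record form and one extra run of the primary model. The change needs to be in place before enrolment.
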